### Qualitative analysis

Narrative data will be analysed using thematic and content analysis. Thematic analysis will identify and describe features within the textual data, whereas content analysis will look for frequency of occurrence of these features. Qualitative analysis will include repeated readings of the text to enable familiarisation with the data, noting preliminary features and patterns of interest, coding the transcripts, adding and modifying codes, and collating data relevant to existing codes until no new codes emerge
[52]. The following textual data will be analysed:

1. Patients’ narrative responses on the screening questionnaire to provide an overview of commonly presenting features of depression/anxiety in primary care for patients seeking computerised therapy.

2. Clinical written records to identify staff rationale for decision-making on suitability and prognosis based on patients’ responses to a standardised questionnaire and after a telephone assessment interview.

3. Recorded sessions and written clinical records from support staff to identify prominent features in the content and delivery of different types of support.

4. Researcher records to identify reasons why patients did not take up cCBT pre-randomisation or dropped out post-randomisation.

5. Recorded exit interviews to identify aspects of cCBT or the adjunct support that patients considered relevant or helpful, or hindering or missing, and any suggestions they may have to improve the study or the intervention.

### Economic evaluation

To establish the cost-effectiveness of clinicians vs. assistants offering brief vs. extended support, we will combine the effects and costs of each of the four support modes (brief-clinician vs. brief-assistant vs. extended-clinician vs. extended-assistant support). Effects will be measured using both the WSAS and the EQ-5D. Cost will be estimated by assigning appropriate unit costs to resources used by patients (therapist contact time, cCBT use, medication use, GP consultations, in-patient and out-patient care, etcetera) before, during and after the interventions. All costs will be calculated in UK £ Sterling using both internal sources (for example, the relevant local organisations’ finance departments) and external sources (for example, Personal Social Services Research Unit (PSSRU)-health and social care costs
[53]). We will estimate cost-effectiveness from the perspective of the NHS and social services according to NICE guidelines
[41]) and also from a broader societal perspective (encompassing for example, patient travel costs, lost productivity and other support received).

If one support mode is shown to be less costly and more effective than all others, determining the most cost-effective support mode will be straightforward, as that support mode would dominate others. Alternatively, the incremental cost per unit of effect will be estimated for each support mode, and the resulting incremental cost-effectiveness ratio (ICER) will be assessed in relation to a range of cost-effectiveness thresholds. To characterise the level of uncertainty in decision-making based on the cost-effectiveness analysis, we will present economic data based on the cost-effectiveness acceptability curve (CEAC) and cost-effectiveness acceptability frontier (CEAF)
[54].

Additionally, sub-group analysis (severe vs. mild/moderate depression or anxiety; referrals from GPs vs. mental health professionals) will be conducted in order to assess how the costs and effects of different modes of support for cCBT vary across different patient groups. Sensitivity analysis will assess the robustness of conclusions to key assumptions that are made within the economics analysis (for example, the level of payment for clinicians or assistants employed). Finally, we will estimate the budgetary impact for the NHS of the population-wide long-term implementation of the most cost-effective mode of individualised support for cCBT.

### Public & patient involvement

A focus group involving public and service user representatives was set up with help from the Patient and Public Involvement in Research (PPIRes) at the local Primary Care trust (NHS Norfolk), to discuss cCBT implementation and patient recruitment. This focus group reviewed some of the study documents (such as the patient information sheet, screening questionnaire and invitation letter) and made recommendations for their improvement and dissemination. Two of the focus group members have been participating in the study trial management group and steering committee. The same members will be actively involved in the interpretation and dissemination of the study’s findings.

### Ethical issues

Approvals were granted by a regional NHS Research Ethics Committee and the Research & Development (R&D) departments of the relevant NHS Trusts. Patient consent is obtained by post. Patients are advised to return the consent form and self-referral questionnaire by post and not by email, to protect confidentiality. Patients can withdraw from the study at any point, without providing a reason, but data collected up to their withdrawal will still be used. Patients retain cCBT access for 24 weeks even if they choose not to speak to the support staff. If a patient needs further treatment upon completion of the study, research staff can directly make a referral to the local psychological therapies service or discuss treatment options with the patient’s GP.

Patients’ research data are stored on a password-protected laptop. Information recorded on the cCBT system can only be accessed by the Chief Investigator, the study’s research administrator and the individual member of staff who offers support to each patient. The support staff do not have access to any named individual feedback about experiences of therapy. Anonymised electronic data (such as demographic information, clinical outcome ratings, extracts from patient interviews and therapist field notes) are accessible only by research and clinical staff involved in the study. Digital recordings are wiped once the transcribed data are stored safely and all identifying information is omitted from transcripts. Archive copies of postal questionnaires and transcripts will be retained for 10 years and then disposed of in accordance with the University and NHS guidelines.

## Discussion

### Methodological considerations

The factorial design of our study increases its efficiency by allowing the concurrent investigation of two different types of support for cCBT, that is, how a clinician compares to an assistant and how brief support compares to extended support, with a single sample of participants. For this, the proposed sample size of 200 randomised patients, with the aim of retaining and analysing data from 140 participants, will be adequate to detect a difference between brief and extended support (for both clinician and assistant) and between clinician and assistant (for both brief and extended support). We will estimate the interaction effect between the two different types of support, but the study is not powered to test it significance unless it is very large.

Most factorial RCTs assume that there is no interaction between their two studied interventions and the presence of strong interactions may lead to loss of power for detecting the main effects of the interventions. This study is not powered to detect an interaction between our interventions, unless this interaction is very large. Whilst a detectable interaction between the duration of support and the person giving support will be interesting from a clinical perspective and potentially informative for health service delivery, it will affect the way we interpret our main effects.

### Practical considerations

Difficulties with patient recruitment and retention in computer-based interventions are reflected in the low take-up and high attrition rates reported in the literature
[13,17,55]. Moreover, this study includes people with depression, a condition which by definition impairs motivation and may make it more difficult for patients to start or continue with therapy. To maximise recruitment and take-up rates, we have kept our exclusion criteria very broad (patients could have any other concurrent treatments and there was no upper cut-off for depression severity). We have also introduced flexible ways of receiving referrals into the study (by telephone, email, text or post from various sources including GPs or any other health professionals, and by public adverts).

To prevent drop-outs and maximise cCBT usage and data completion, we have offered participants the option of accessing cCBT at home or in public places (libraries, cafes, etcetera.) and of having adjunct support or returning their questionnaires and giving us feedback via email, post or telephone. To date, all outcome measures have been received by post, all participants accessed cCBT from home and all support sessions took place by telephone with the exception of appointments or cancellations, which tend to happen via email or text.

An important point of consideration for our study is that there is no face-to-face contact with the researchers or the clinicians at any point because all referrals, assessments, interventions and data collection are completed remotely via telephone, computer or post. This lowers the research costs (for example, there is no need to rent rooms or to travel to people’s homes, or to employ extra people to allow for loss of time because of travelling) and reflects routine conditions in the UK primary care psychological therapy services, in which patient assessments and cCBT delivery are completed mostly by telephone as part of so-called step 2 interventions.

We cannot tell whether the lack of face-to-face contact may compromise take-up, completion or effectiveness of cCBT or whether the addition of face-to-face contact could have enhanced those. Face-to-face support has been shown to have better outcomes than telephone support in self-help for bulimia
[23], and lack of face-to-face contact was the reason given by a third of all drop-outs from an online intervention for post-traumatic stress disorder
[56]. On the other hand, telephone-delivered CBT (as a stand-alone intervention and not as support to a computer system) was found to be as effective and acceptable as face-to-face CBT for obsessive-compulsive disorder (OCD)
[57] and for chronic fatigue syndrome
[58].

### Potential implications

With depression being one of the most burdensome health problems worldwide, there is an increasing interest in technology-mediated interventions, such as cCBT, which can be accessed relatively easily in the community by large numbers of people. Literature suggests that personal support may be a necessary adjunct to cCBT to keep people motivated or to improve outcomes, but we do not know who should provide this support and for how long. The results of this study could indicate whether patients benefit more from extended vs. brief support or from support offered by a clinician or an assistant. The study will also indicate whether brief-assistant support may appear more economical but may compromise outcomes and include hidden costs, and whether the perceived more expensive option of extended clinician support can be offset by better clinical outcomes and greater patient satisfaction. Finally, the study can lead to recommendations as to how telephone support could be tailored to suit different patients and which mix of staff expertise and support duration could optimise clinical outcomes and patient satisfaction with cCBT within the current budget constraints of healthcare providers.

## Trial status

Patient recruitment was ongoing at the time of manuscript submission and stopped in June 2012. Data collection will continue until September 2012.

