## Methods/design

### Design

This is a two-by-two factorial RCT. Patients are randomly allocated to an eight-session cCBT programme supported either by a clinician or by an assistant, each offering either brief or extended phone support. The four randomly-created groups are: brief-clinician, brief-assistant, extended-clinician or extended-assistant support for cCBT. The primary follow-up point is at 3 months post-randomisation and the secondary follow-up point is at 6 months post-randomisation.

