### Data collection

Baseline demographic and clinical characteristics are obtained by the self-referral questionnaire which is completed by patients and posted to the research team before randomization. The self-referral questionnaire has been suitably adapted for the purpose of this study from its previous validated version
[33]. The questionnaire has nine sections which elicit quantitative and narrative data about patients’ symptoms, computer literacy, lifestyle, past and present treatments including medication, and therapy goals and preferences for therapist-delivered interventions vs. computerised self-help.

Data on clinical outcomes, resource use and patient experiences are collected in two ways: both by post and electronically. Postal questionnaires are sent to patients at baseline (randomization) and then at weeks 12 (primary end-point) and 24 (follow-up) post-randomization with instructions to complete them and return to the research team. Electronic data are collected automatically by the cCBT system during each cCBT session. The timing of electronic data collection is recorded by the cCBT system but it varies according to the frequency with which patients log into it.

Narrative data are also collected during a 15 to 30 minute assessment with the patient pre-randomization, as part of support sessions by the clinician and the assistant, and during a 15 minute telephone interview, which asks about patient views and experiences of using a computerised self-help system and of having telephone support at 12-weeks post-randomization, by the study’s research associate (JM).

Below we give a detailed description of individual data collection tools and justification for their inclusion in the study. All standardised measures are self-reported and are collected independently of the staff proving telephone support; there are no observer-rated outcomes so there is no need for blinding.

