### Statistical analysis

Descriptive statistics will summarise demographic and clinical features of those referred, those randomised, those who complete the intervention (at least 5 cCBT sessions) and those who complete at least one set of post-baseline outcome measures. The same variables and baseline values of the outcome measures will be compared between brief and extended support, and between clinician and assistant at baseline. Where large differences exist, these variables will be included as potential confounders. Our primary analysis will be based on the first batch of completed postal questionnaires returned by the patients. These are posted out to the patients at 12 weeks post-randomisation but the timing of receiving completed questionnaires from the patients is variable. The time of receipt is recorded and may be included as a covariate.

Linear models will be used to estimate the main effects of the two treatments. An estimate and confidence interval for the interaction term will be obtained. Corresponding adjusted estimates will be obtained adjusting for baseline only, and for baseline and the potential confounders identified at baseline. Effect sizes will be calculated using Cohen’s d
[49]. The number of patients showing clinically significant and reliable change
[50] will be reported where possible. C-PAS and T-PAS will be compared for each group using mixed-effects models and their similarity will be assessed using intra-class correlation.

The primary analysis will include patients in the groups to which they had been randomly assigned regardless of the actual treatment they have received. The primary analysis will include non-missing data only, but the baseline characteristics of missing and non-missing values will be compared to assess the pattern of missing data. Further, as recommended by Altman
[51], sensitivity analyses will be performed by employing multiple imputation techniques. Where a few items within a scale are missing for an individual participant we will impute using that person’s scale average.

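### The stated dates (recruitment to June 2012, data collection to September 2012) cannot deliver the week-24 follow-up planned for all patients

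*Protocol article*

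**What the plan says.** The Design section sets two time points, without exception for late entrants: "The primary follow-up point is at 3 months post-randomisation and the secondary follow-up point is at 6 months post-randomisation". The Data collection section gives the matching postal schedule, with questionnaires at baseline and then "at weeks 12 (primary end-point) and 24 (follow-up) post-randomization". That schedule covers clinical outcomes, resource use and patient experiences.

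The only calendar in the article is in Trial status, which says that recruitment "stopped in June 2012. Data collection will continue until September 2012". No day of the month is given for either.

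The Statistical analysis section adds, about the 12-week questionnaires, that "the timing of receiving completed questionnaires from the patients is variable". The time of receipt is recorded and may be used as a covariate. No closing window for returns is given.

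**The concern.** From June to September is about three months, while the planned follow-up is about six. If collection closes as stated, patients who entered late have no opportunity to supply week-24 data, whatever their willingness to do so.

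Secondary 24-week clinical outcomes would be lost for these patients, along with the later part of their resource use. The Economic evaluation section needs costs before, during and after the interventions. Telephone support may run for up to 24 weeks (Telephone support) and programme access lasts 24 weeks (Ethical issues). For a June entrant, a September close therefore comes before the end of the possible support and access period.

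Attrition is also an outcome here, as part of acceptability in the third primary objective. A patient whose week-24 date never arrived within the collection period is different from one who did not return a form. The article does not say how the two would be told apart.

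**Working it through.** **Inputs**
- Recruitment stop: June 2012, day not given, so 1 to 30 June (Trial status).
- End of data collection: September 2012, day not given, so 1 to 30 September (Trial status).
- Assessments at 12 weeks = 84 days and 24 weeks = 168 days, both counted from randomisation (Data collection).
- Assumption: the last randomisation falls on the day recruitment stops. Randomisation follows receipt of the postal consent form and baseline questionnaires (Treatment allocation). If recruitment in Trial status means referral, the last randomisations are later and the gap is wider.

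**Step 1. Due dates for June entrants** (randomisation date + 84 or + 168 days)

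| Randomised | Week 12 due | Week 24 due |
|---|---|---|
| 1 June 2012 | 24 August | 16 November |
| 15 June 2012 | 7 September | 30 November |
| 30 June 2012 | 22 September | 15 December |

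June plus 12 weeks agrees with a September end. June plus 24 weeks does not.

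**Step 2. Time available against 168 days** (end of collection − randomisation date)

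| Randomised | Collection ends | Days available | Short of week 24 | Margin after week 12 |
|---|---|---|---|---|
| 1 June | 30 September | 121 | 168 − 121 = 47 | 121 − 84 = 37 |
| 30 June | 30 September | 92 | 168 − 92 = 76 | 92 − 84 = 8 |
| 1 June | 1 September | 92 | 168 − 92 = 76 | 92 − 84 = 8 |
| 30 June | 1 September | 63 | 168 − 63 = 105 | 63 − 84 = −21 |

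The shortfall at week 24 is positive in every row, from 47 to 105 days.

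**Step 3. Latest randomisation date that still reaches each assessment** (end of collection − 168 or − 84 days)

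| Collection ends | Last date for week 24 | Last date for week 12 |
|---|---|---|
| 1 September | 17 March 2012 | 9 June 2012 |
| 15 September | 31 March 2012 | 23 June 2012 |
| 30 September | 15 April 2012 | 8 July 2012 |

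These dates allow no time for postal return, so the practical cut-offs are somewhat earlier.

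**Step 4. Length of recruitment affected.** At the least, this runs from 16 April to 1 June inclusive (15 + 31 + 1 = 47 days). At the most, it runs from 18 March to 30 June inclusive (14 + 30 + 31 + 30 = 105 days). Turning this into a number of patients needs an accrual rate, which the article does not give.

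**The case against.** The strongest reply is that Trial status is a two-sentence administrative note and that its September date refers to completion of the primary follow-up. Step 1 makes this plausible, since June plus 12 weeks ends between 24 August and 22 September. The 12-week time point is also the primary one and the basis of the sample size. But the article does not say that September means the 12-week assessment, nor that late entrants have no week-24 assessment. If that was the intention, the unqualified 24-week schedule in Design and Data collection is overstated. This is also not detail left to a fuller document, because two statements in the same article are incompatible.

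Three stronger readings are tempting, and the document does not support them.

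- A reader might infer that the last 12-week returns are cut short. With a 30 September close, every June entrant reaches week 12, with 8 to 37 days left for return. Returns would be lost only if collection closed earlier in September, if forms came back more slowly than that margin, or if randomisation ran past early July. None of these is stated, so this is a risk and not an established loss.
- A reader might infer that late entrants will be counted as drop-outs. No section says so. The plan records reasons for drop-out, compares patients with and without missing data, and adds multiple imputation. Rules for denominators may sit in an analysis plan that is not shown.
- A reader might infer a biased comparison between arms. The cut-off depends on the calendar date of entry, and allocation is in blocks of 32 with eight patients per arm. The loss should therefore fall roughly equally across arms. The expected cost is precision at 24 weeks and an unclear attrition figure, with no evident distortion of the treatment effect.

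**Conclusion.** The contradiction stands. Under the dates as written, no patient randomised after about 15 April 2012 can reach week 24, and the cut-off is as early as 17 March if collection closes on 1 September. The last June entrant misses it by 47 to 105 days, depending on which days in June and September are meant. This rests only on the two stated months and the 168-day schedule; the day-of-month uncertainty changes the size and not the conclusion.

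The consequence is limited to the secondary 24-week clinical outcomes, the resource-use data collected at the same time and the 24-week attrition figures. The primary 12-week end-point is largely compatible with the dates. How many of the planned 200 randomised patients are affected cannot be computed from the article; it could be few or many. The point is an inconsistency that needs correcting and does not threaten the primary analysis.

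**What to change.** Reconcile Trial status with Design and Data collection in one of two ways.

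1. Keep postal collection open until the last randomised patient's week-24 date, which is 16 November to 15 December 2012 for June entrants, plus time for return. The cost is small: about three more months of posting and logging questionnaires.
2. State that patients randomised after a named date have 12-week follow-up only. Restate what the 24-week clinical and economic analyses cover. In the 24-week attrition figures, report these patients as administratively censored, separately from drop-outs. This costs only a corrected statement, but accepts the loss of their 24-week data.

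In either case, give the actual closing date and say whether June 2012 refers to the last referral or the last randomisation. No change of analysis model is needed for this point, since multiple imputation is already planned as a sensitivity analysis.
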